**Figure 1 F1:**
[figure not shown]
Protocol for selection participants. CHM = Chinese herbal medicine, HSPN = Henoch–Schönlein purpura nephritis.

### Ethical issues

2.3

This study registered in ClinicalTrials.gov with approval number NCT02878018 and was approved by the Ethics Committee of the Institutional Ethics Board of the Affiliated Hospital of Liaoning University of Traditional Chinese Medicine (Shenyang, China; Approval number: 2016CS(KT)-002-01). After completing a baseline description of the study to the enrolled subjects, written informed consent will be obtained from each of patients.

### Participants

2.4

#### Diagnosis criteria

2.4.1

Diagnosis and treatment guidelines for HSPN was based on the criteria in the 2000 Congress of Chinese Pediatric Society.^[21]^

#### Inclusion criteria

2.4.2

1.A diagnosis of HSPN according to the diagnosis criteria.2.Age: 5 to 18 years old (including 5 and 18 year old).3.The clinical classification of HSPN includes isolated hematuria, insolated proteinuria, hematuria with proteinuria, and acute glomerulonephritis.4.The ability to provide detailed connection and complete a follow-up.5.The ability to understand and sign a written informed consent.

#### Exclusion criteria

2.4.3

1.HSPN with renal insufficiency.2.A clinical classification of HSPN that includes nephritic syndrome, rapidly progressive glomerulonephritis, and chronic glomerulonephritis.3.Suffering from serious complications, such as respiratory, digestive, hematological, or liver diseases.4.Tumor, infectious diseases, or mental disorders.5.Allergic to TCM use.6.No prescribed medication, poor compliance, or incomplete data affecting the efficacy and safety of these judgments.7.A history of another clinical trial in the previous 2 weeks.8.No consent form signed.

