### Sample size calculation

2.6

According to the response rates of treatment, the cohort 1 and the cohort 2 were 53% and 40%, respectively. It was estimated that 250 patients of each group would be sufficient to achieve 90% power in detecting treatment differences, based on a 2-sided alpha at a significance level of 0.05. Meanwhile, considering a dropout rate of 20%, we concluded that a total of 300 patients for each cohort would need to be recruited to ensure significant results.

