### Safety assessment

2.7

For the sake of participant safety, the following biological indicators will be monitored and watched throughout the trial: blood routine, liver function (AST, ALT), renal function (BUN, Cr), and electrocardiography (ECG). Any unexpected symptoms and signs or feelings of discomfort in patients will be recorded as adverse events. For each adverse event, the starting date, ending date, degree, relationship to the trial and potential to trigger patient drop-out from the study will be carefully recorded and considered. If an adverse event occurs, the patient will be monitored until his/her adverse event disappears.

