### Statistical analysis

2.9

The statistical analysis will be conducted by a statistician of the Institute of Basic Research in Clinical Medicine, China Academy of Chinese Medical Sciences, Beijing, China. The statistician is blinded to the entire trial and will use SAS 9.1.3 (SAS Institute, Cary, NC, USA) and SPSS Version 13.0 (SPSS Inc., Chicago, IL) software. To test the hypotheses about associations between baseline risk factors and HSPN incidence, hazards ratios will be computed using the Cox proportional hazard regression models. Baseline differences between the groups will be assessed with the use of Student's *t*-test for normally distributed continuous variables and the nonparametric Mann–Whitney *U*-test for non-normally distributed variables. Comparisons between the groups will be conducted using an analysis of covariance (ANCOVA) with the baseline as the covariate. For efficacy analysis, changes from the baseline to the endpoint of treatment in scores will be tested with repeated measured analysis of variance (ANOVA). Within each group, differences will be assessed with paired t-test for normally distributed data and the Wilcoxon signed-rank test for non-normally distributed data. Safety will be assessed by participant compliance and adverse events. For analysis of the final dataset, missing data will be filled in using the last observation carried forward (LOCF) approach. A *P* value <.05 is considered significant.

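### Exclusion criterion 6 permits removal of children for non-compliance or incomplete data that arise after treatment starts, and it contradicts the dropout allowance and the missing-data rule

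*Protocol article*

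**What the plan says.** Section 2.4.3 (Exclusion criteria), item 6, excludes children for "No prescribed medication, poor compliance, or incomplete data affecting the efficacy and safety of these judgments". No time point is attached, and no other section restricts the item to screening.

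Three other sections bear on the same children:

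- Section 2.6 (Sample size calculation) raises recruitment from 250 to 300 per cohort, "considering a dropout rate of 20" per cent.
- Section 2.9 (Statistical analysis) states that "missing data will be filled in using the last observation carried forward (LOCF) approach" and that "Safety will be assessed by participant compliance and adverse events".
- Section 2.7 (Safety assessment) states that for each adverse event the "relationship to the trial and potential to trigger patient drop-out from the study will be carefully recorded and considered".

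The cohorts are formed by the treatment received, not by randomisation (section 2.2). Treatment lasts 12 weeks and follow-up a further 12 months (sections 2.1 and 2.8). The primary outcomes are remission rate and recurrence rate (section 2.5.1).

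**The concern.** An eligibility criterion should rest on facts available when the child enters. Incompleteness that affects the efficacy and safety judgments is a fact about the treatment and follow-up record, so it arises later. Poor compliance is also a later fact unless it is confined to past behaviour. If the item is applied as written, an enrolled child who stops treatment or leaves too little data can be declared ineligible afterwards.

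Stopping and missing data may depend on how the child is doing or on side effects. Removing such children selects the analysed cohorts on post-baseline events. The comparison is not randomised and runs for well over a year, so there is ample room for such removal and no design feature that would make it balanced. Both primary outcomes and the adverse-event rates are exposed.

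**Working it through.** **Step 1: set the sections side by side.** Take a child who starts treatment, stops part-way through the 12 weeks and has no usable later assessments.

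| Section | Status of this child |
|---|---|
| 2.4.3, item 6 | Not eligible |
| 2.6 | A recruited cohort member, within the expected 20% dropout |
| 2.9, missing data | In the final dataset, with the last observation carried forward |
| 2.9, safety | Someone whose compliance is to be assessed |

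The conflict is sharpest with section 2.9: a child who has been excluded needs no imputation, and compliance is poorly measured in a cohort from which poor compliers have been taken out. Section 2.6 does not say whether dropouts are analysed, but it does treat them as recruited. The document does not say which status prevails.

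**Step 2: the plan's own figures.** The planning rates are such that "the cohort 1 and the cohort 2 were 53% and 40%, respectively", a difference of 13 points. The recruitment target is 250 × 1.20 = 300 per cohort. A 20% loss from 300 leaves 300 × 0.80 = 240. At 53% versus 40%, two-sided alpha 0.05, power is 81.7% with 240 per cohort and 89.3% with all 300. (The stated inputs give 308 per group for 90% power, not 250. That is a separate matter, and this point does not depend on it.)

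**Step 3: possible bias in remission.** The document gives no removal rates and no outcome rates for removed children, so the values below are assumptions. Let p be true remission, the same in both cohorts; e the share removed; q remission among those removed. Then

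retained remission = (p − e·q) / (1 − e).

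With p = 0.45 and q = 0.25:

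- e = 0.10: (0.45 − 0.025) / 0.90 = 47.2%
- e = 0.20: (0.45 − 0.050) / 0.80 = 50.0%
- e = 0.25: (0.45 − 0.0625) / 0.75 = 51.7%

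| Removal, one cohort vs the other | Observed remission | False gap |
|---|---|---|
| 20% vs 20% | 50.0% vs 50.0% | 0 |
| 20% vs 10% | 50.0% vs 47.2% | 2.8 points |
| 25% vs 10% | 51.7% vs 47.2% | 4.4 points |

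The 25% share exceeds the only loss figure in the document, 20%.

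**Step 4: direction, and equal shares.** The error within a cohort is e(p − q)/(1 − e). It is positive if removed children do worse than average, negative if they do better, and zero if removal is unrelated to outcome. Equal shares protect the contrast only if q is also equal. For example, with p = 0.40, 20% removed from each cohort, q = 0.20 in cohort 1 and q = 0.40 in cohort 2, observed rates are (0.40 − 0.04)/0.80 = 45% and (0.40 − 0.08)/0.80 = 40%, a false gap of 5.0 points. At 240 per cohort, a gap of that size is declared significant about 20% of the time, against a nominal 5%.

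**Step 5: possible bias in safety.** Assume a true adverse-event risk of 10% and 20% removed. The observed risk is (0.10 − 0.20·q)/0.80, where q is now the risk among removed children. For q of 10%, 20% and 30% it is 10%, 7.5% and 5%. Safety is understated only if removed children carry a higher risk.

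**The case against.** The best defence is that item 6 sits in a list of screening criteria and should be read as one. Being without prescribed medication is knowable at entry, and poor compliance can mean compliance to date. This part stands: it would be too strong to say that compliance can never be judged at enrolment. The defence does not reach the incomplete-data clause, which has no natural screening meaning. A prospective check on follow-up already exists as inclusion criterion 4 (section 2.4.2).

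A second defence is that carrying observations forward, the dropout allowance and the telephone contact after a missed follow-up visit (section 2.8) all point to keeping children with gaps. That is fair, and it means a reader should not infer that every child who misses a visit is removed, or that the same children are certain to be both excluded and imputed. But it shows an unresolved contradiction and does not cure the item.

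A third defence is that analysis sets may be defined in a document not shown. A missing definition would be no finding. Here the article states a rule that conflicts with its other stated rules.

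A reader might also infer that adverse events leading to non-compliance vanish from the study. Section 2.7 does not support that: events and their link to drop-out are recorded, and the child is monitored until the event resolves. What remains open is whether such a child stays in the safety analysis.

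**Conclusion.** The point holds in a limited form. Item 6, as worded, permits children to be removed after baseline in a non-randomised comparison, and it contradicts sections 2.6 and 2.9. Bias in a cohort's own remission, recurrence or adverse-event rate requires removal to be related to that outcome. Bias in the contrast between cohorts also requires the removal pattern, in share or in type of child, to differ between them.

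The size cannot be derived from the document. On the assumptions of 45% true remission and 25% among removed children, it runs from 0 (equal removal) through 2.8 points (20% versus 10%) to 4.4 points (25% versus 10%), against a planned difference of 13.

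Two stronger readings are tempting. One is that safety is understated as a matter of fact. Section 2.7 links adverse events to drop-out, so this is plausible, but no event rate for removed children is given and it is not certain. The other is that the bias must favour one cohort, or that children have already been removed. The document reports no removals and no compliance or tolerability rates by cohort, and children who improve may also stop attending.

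**What to change.** Limit item 6 to facts known at screening: delete the incomplete-data clause and restrict poor compliance to history before enrolment. State that every enrolled child who started the cohort-defining treatment is analysed, for efficacy and for safety, in the cohort set at that start. Keep the compliant, complete-data subset as a sensitivity analysis only. Bring sections 2.4.3, 2.6 and 2.9 into agreement on what happens to a child who stops or has gaps in the record. If any enrolled child has been removed under this item, keep that child in the main analysis.

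The cost is a change of wording and of the analysis set, with no new procedures. The downside is more missing data to handle, since children with incomplete records now stay in.

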### Outcome measures

2.5

#### Primary outcomes

2.5.1

The primary outcomes of this study are remission rate and recurrence rate of HSPN.

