### Study design

2.1

This large, prospective, multicenter cohort study is being conducted in 3 institutions between May 2015 and May 2020. Six hundred participants are recruited and divided into 2 cohorts, with 300 individuals per cohort. All cohorts will undergo a 12-week treatment and a 12-month follow-up period. Participants will be asked to visit the clinicians every 2 weeks during the treatment period and once a month during the follow-up period. The feasibility and preciseness of the whole process are supervised by 1 to 2 supervisors.

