In this trial, we intend to assess the efficacy and advantage of the use of CHM for the treatment of children with HSPN. We hypothesize that CHM will be an effective and safe way to treat HSPN patients and to reduce the recurrence rate.

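### Two unordered primary outcomes share one undivided P<.05, and the single sample size, which fits remission at best, does not establish 90% power for recurrence

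*Protocol article*

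**What the plan says.** All references are to the protocol article.

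- Section 2.5.1: "The primary outcomes of this study are remission rate and recurrence rate of HSPN". Neither outcome is placed first, and success on both is not required.
- Section 2.9 closes with one general rule: a P "value <.05 is considered significant". It draws no distinction between outcomes.
- Section 2.6 gives one calculation: "According to the response rates of treatment, the cohort 1 and the cohort 2 were 53% and 40%, respectively". It concludes that "250 patients of each group would be sufficient to achieve 90% power in detecting treatment differences". The error rate behind this figure is stated once and is not shared between outcomes: "based on a 2-sided alpha at a significance level of 0.05". It then recruits 300 per cohort: "considering a dropout rate of 20%, we concluded that a total of 300 patients for each cohort would need to be recruited". It does not say which primary outcome the response rate stands for, and it gives no recurrence rate.
- The Discussion closes with recurrence as an aim of its own: "We hypothesize that CHM will be an effective and safe way to treat HSPN patients and to reduce the recurrence rate".

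**The concern.** With two primary outcomes and the full 0.05 available to each, a reader may accept a positive result on either one as the study's primary finding. The error rate for that claim is then not the 5% on which Section 2.6 is built.

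The sample size serves the two outcomes unequally. A rate that is higher with herbal medicine (53%) than without (40%) is a good outcome, so it can stand for remission but not for recurrence. Recurrence is named both as a primary outcome and in the hypothesis, yet it has no planning rate and no power. In the ordinary sense of the word, a child must remit before relapsing, so the number at risk of recurrence may be well below the number enrolled. A null result on recurrence could then be read as evidence of no effect, and a positive one as having come from a test with 90% power. The article supports neither reading.

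**Working it through.** **Inputs.** From the article: two primary outcomes (2.5.1); threshold 0.05 (2.9); 53% vs 40%, two-sided 0.05, 90% power, 250 evaluable and 300 recruited per cohort, 20% dropout (2.6). Assumptions of this check: response means remission, only remitters can recur, and the recurrence rates shown below.

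**1. The plan's own figure.** The pooled-variance formula for two proportions with 53%, 40%, two-sided 0.05 and 90% power gives 308 per cohort, not 250. One-sided 0.05 gives 251. With 250 per cohort, two-sided power is 83.2%. This is a separate sizing problem. It matters here only because it must not be counted as a cost of multiplicity.

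**2. False primary claims.** Two tests, each at 0.05:
- independent: 1 − 0.95² = 0.0975, or 9.75%;
- upper bound whatever the dependence: 0.05 + 0.05 = 10%.

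**3. What an alpha split would cost for remission.**

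| Per cohort | Power at 0.05 | Power at 0.025 |
|---|---|---|
| 250 (plan's evaluable number) | 83.2% | 75.1% |
| 240 (300 × 0.8) | 81.7% | 73.2% |

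Splitting alpha costs about 8 points at either size (83.2 − 75.1 = 8.1; 81.7 − 73.2 = 8.5). The rest of the gap to 90% comes from the sizing problem in step 1.

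**4. Children who could recur.** 300 × 0.8 = 240 per cohort. 240 × 0.53 = 127.2 and 240 × 0.40 = 96.0. With the plan's 250 the numbers are 132.5 and 100.

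**5. Power for recurrence among 127.2 vs 96, two-sided 0.05.** Power = Φ[(d − 1.96·SE₀)/SE₁], with SE₀ from the pooled rate and SE₁ from the separate rates.
- 20% vs 30%: pooled rate = (127.2 × 0.20 + 96 × 0.30)/223.2 = 0.243; SE₀ = 0.0580; SE₁ = 0.0587; (0.10 − 0.1137)/0.0587 = −0.23; power 41%.
- 10% vs 30%: pooled rate 0.186; SE₀ = 0.0526; SE₁ = 0.0538; (0.20 − 0.1031)/0.0538 = 1.80; power 96%.

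| Assumed recurrence, cohort 1 vs cohort 2 | Power |
|---|---|
| 20% vs 30% | 41% |
| 27% vs 40% | 54% |
| 20% vs 35% | 71% |
| 20% vs 40% | 90% |
| 10% vs 30% | 96% |

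**6. What either denominator for recurrence would do.** These are illustrations, because the article does not fix a denominator.
- Among remitters: suppose the extra 13% who remit in cohort 1 recur at 40% and all other remitters at 20%. Cohort 1 then shows (0.40 × 0.20 + 0.13 × 0.40)/0.53 = 24.9% against 20% in cohort 2, with no effect of treatment on recurrence.
- Among all enrolled: an equal 30% risk among remitters gives 0.53 × 0.30 = 15.9% against 0.40 × 0.30 = 12.0%. The cohort with more remissions looks worse.

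**7. Can sustained remission stand in for recurrence?** Assume an identical 25% recurrence in both cohorts. Sustained remission is 0.53 × 0.75 = 39.75% vs 0.40 × 0.75 = 30.0%. The test is significant about 61% of the time at 240 per cohort (63% at 250), although recurrence does not differ at all.

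**The case against.** The strongest reply is that this is a condensed article. An order of outcomes, an alpha rule or a denominator for recurrence could stand in a full protocol or SAP that is not shown. The threshold in Section 2.9 is a generic closing sentence and does not say that either outcome alone supports a claim. If both had to be significant, no alpha adjustment would be needed. The Discussion also looks ahead to further confirmatory studies, and in a non-randomised cohort strict error control carries less weight than in a pivotal trial. All of this limits the weight of the point. It does not remove it: two primaries without rank, one undivided threshold and one calculation at undivided alpha are what this document fixes, and its hypothesis puts recurrence forward as a claim of its own.

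Two stronger readings are tempting and are not supported.

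- *A reader might infer that the recurrence comparison is underpowered and not comparable between cohorts.* The article never says that recurrence will be analysed among remitters, and it does not equate response with remission. The 53% and 40% are planning values, not a ceiling on how many children can remit, and the 12-month follow-up leaves room for later remission. Power ranges from 41% to 96% over the assumed pairs, so low power cannot be stated as fact. Selection on remission is a hazard of one possible analysis. The cohorts are formed by treatment received, so comparability is not secured by design for remission either.
- *A reader might set 73% power at a split alpha against the stated 90% and blame multiplicity for the whole gap.* Most of that gap is the separate sizing error: at 240 per cohort, power is already only 82% with undivided 0.05.

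**Conclusion.** The point holds in a limited form and should be addressed. As the outcomes and threshold are written, the chance of at least one false primary claim is 9.75% for independent tests and at most 10%, against a nominal 5%. This rests on either outcome being able to support a claim on its own; a rule requiring both would remove the problem, but the article states none.

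The stated 90% power belongs to remission at best and is not established for recurrence. How far recurrence falls short, if it does, cannot be known from the article. The range in step 5 depends on three assumptions: response means remission, only remitters are at risk, and the recurrence rates are those assumed. The comparability concern is conditional on an analysis among remitters.

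**What to change.** - **Sections 2.5.1 and 2.9:** name remission as the first primary outcome, tested at two-sided 0.05. Test recurrence formally, also at two-sided 0.05, only if remission is significant. This fixed sequence holds the family-wise error at 5% without splitting alpha, so remission does not bear the loss of about 8 points in step 3.
- **Section 2.6:** state that the 53% vs 40% calculation applies to remission and that power for recurrence is not established.
- **If recurrence is compared among remitters:** report it with a confidence interval and the caveat that this subset is selected after treatment starts, so adjustment for baseline does not make the two groups comparable.
- **Sustained remission in all enrolled children** may be added as a supportive outcome. It must be labelled a composite driven partly by remission. Step 7 shows why it cannot serve as the test of recurrence.

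Cost: no new data and no larger sample, but this is more than an edit of wording. The abstract reports the 600 children as already recruited and the study is registered, so the ordering should be recorded as a dated amendment before the outcome data are analysed by cohort. The downside is that no formal recurrence claim can be made if remission is not significant.

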#### Secondary outcomes

2.5.2

1.Symptom improvement (such as urine erythrocyte, urine protein, etc)2.Adverse events.

Each symptom or sign will be given a score, and the sum of all scores will be recorded in Table 1.

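### The symptom-score comparison between non-randomised cohorts does not adjust for clinical class, although children with a single urinary sign have less room to improve than those with two

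*Protocol article*

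**What the plan says.** Section 2.5.2 lists "Symptom improvement (such as urine erythrocyte, urine protein, etc" as a secondary outcome and adds: "Each symptom or sign will be given a score, and the sum of all scores will be recorded in Table 1". Table 1 is not visible in the text at hand.

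Inclusion criterion 3 (section 2.4.2) admits "isolated hematuria, insolated proteinuria, hematuria with proteinuria, and acute glomerulonephritis".

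Section 2.2 forms the cohorts by treatment: children taking CHM are cohort 1, and children on WM without CHM are cohort 2. There is no randomisation.

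Section 2.9 compares the groups by "analysis of covariance (ANCOVA) with the baseline as the covariate". For efficacy, "changes from the baseline to the endpoint of treatment in scores will be tested with repeated measured analysis of variance (ANOVA"), and no covariate is named there. Clinical class appears in neither analysis.

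**The concern.** Taken at face value, a child with isolated hematuria has no proteinuria to lose, and a child with isolated proteinuria has no hematuria to lose. On the urinary items of the sum, such children can improve on one sign only. Children with both signs can improve on two, so the expected fall in the score may depend on class even when the treatments are equally good.

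In a randomised trial this would mostly add noise. Here the choice between CHM and WM may go with how the disease presents, so the class mix may differ between cohorts. The cohort with more two-sign children would then show the larger mean fall for that reason alone. What is at stake is a spurious, or masked, difference on the symptom score.

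**Working it through.** The plan gives no figure for this point, so the check is an illustration with stated assumptions.

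**Inputs from the article**
- 250 analysed per cohort and two-sided 0.05 (section 2.6). Only the number analysed is used. As a separate matter, 250 per group gives 83% power for 53% v 40%, not the stated 90%, which needs 308.
- 40%, the cohort 2 response rate (section 2.6), borrowed as the chance that a sign improves, equal in both cohorts (no treatment effect).

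**Assumptions**
- Only the two urinary signs are scored. A sign that is present has grade 1, 2 or 3 with equal chance; an absent sign has grade 0.
- An improving sign falls by one grade. Signs are independent.
- A share f of each cohort has one sign only: 30% in one cohort, 50% in the other.

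**1. Unadjusted change**
- Expected fall: one sign 0.40, two signs 0.80.
- Cohort means: 0.3×0.40 + 0.7×0.80 = 0.68 and 0.5×0.40 + 0.5×0.80 = 0.60. The difference is 0.08 with no treatment effect.
- Variance of the fall: 0.24f + 0.48(1−f) + 0.16f(1−f), which is 0.4416 and 0.4000.
- SE = √((0.4416 + 0.4000)/250) = 0.0580, and 0.08/0.0580 = 1.38.
- Rejection = Φ(1.38 − 1.96) + Φ(−1.38 − 1.96) ≈ 28%.

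**2. Baseline score as covariate**
- Mean baseline score is 2 with one sign and 4 with two, so the cohorts average 3.4 and 3.0, a gap of 0.4.
- Within-cohort variance of baseline: (2/3)f + (4/3)(1−f) + 4f(1−f), which is 1.973 and 2.000, average 1.987.
- Within-cohort covariance of fall and baseline: f(1−f)×0.40×2, which is 0.168 and 0.200, average 0.184.
- Slope = 0.184/1.987 = 0.0926. Adjusted difference = 0.08 − 0.0926×0.4 = 0.043.
- Residual variance = 0.4208 − 0.0926×0.184 = 0.4038. SE = √(0.4038×(2/250 + 0.4²/(500×1.987))) = 0.0574. Ratio 0.75.
- Rejection ≈ 12%. About half of the false difference remains.

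**3. Baseline score and class**
- Within a class the expected fall is the same in both cohorts, so the adjusted difference is 0 and rejection is 5%.

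**4. Milder imbalance, 30% v 40%**
- Means 0.68 and 0.64, difference 0.04. Variances 0.4416 and 0.4224, SE 0.0588, rejection about 10%.
- With the baseline covariate: slope 0.18/2.00 = 0.09, baseline gap 0.2, difference 0.04 − 0.09×0.2 = 0.022, rejection about 7%.

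**5. A different scoring assumption**
- Suppose an improving sign clears completely. The expected fall is then 0.40 × baseline score in every class.
- Unadjusted, 30% v 50% gives a false difference of 0.40×0.4 = 0.16. With E(grade²) = 14/3, the variance is 1.227 for one sign and 2.453 for two. Adding 0.64f(1−f), the cohort variances are 2.220 and 2.000, SE = √(4.220/250) = 0.130, rejection about 23%.
- The fall is linear in the baseline score, so ANCOVA on baseline removes the difference and rejection returns to 5%.

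Simulation of cases 1 to 5 agreed with these results to within about a percentage point. A further simulation of a summed score, with isolated-hematuria shares of 30% v 50%, gave about 26% unadjusted, 13% with baseline only and 6% with class added.

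**The case against.** **The summed score is attainable for everyone.** Every admitted class has at least one urinary abnormality, so no child faces an impossible outcome, and a smaller range in milder children is ordinary variation in severity. The article names ANCOVA on the baseline for the group comparison, which addresses that. Much of this stands: baseline adjustment removes part of the problem in case 2 and all of it in case 5. Whether it removes everything depends on scoring that cannot be seen. It also does nothing for the repeated-measures ANOVA, for which no covariate is named.

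**A stronger reading is tempting.** A reader might infer that urine protein and urine erythrocytes are each tested in all children, so that those without the sign count as failures and dilute the effect. With 53% v 40% among affected children and 30% unaffected, the 13-point difference would shrink to 0.7×13 = 9.1 points and power to 58%, against 69% in affected children only. With no effect, unaffected shares of 30% v 50% would give 0.40×0.7 = 28% v 0.40×0.5 = 20% improved, with rejection near 56%. The documents do not support this reading. The two signs are examples inside a scored sum, and no separate component test, improvement rate or all-children denominator is stated. The 53% and 40% are overall response rates, and the planned methods work on scores. Component denominators are also something an article commonly leaves to the full protocol or SAP. Even if components were analysed in all children, a smaller average effect over everyone enrolled is a legitimate estimand, not an error.

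**Unseen definitions.** The class thresholds come from a cited guideline and the grades from Table 1. If single-sign children can score above zero on the other sign, or if non-urinary items dominate the sum, the effect is smaller. This limits the size, which is why none is claimed.

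**Conclusion.** The point holds in a limited form. Classes with different room to improve, cohorts formed by treatment taken, and a score analysis with no term for class can together produce a difference in score change without a treatment effect. In the illustration, the 5% test rejects 10% to 28% of the time on unadjusted change and between 5% and 12% with the baseline score as covariate, depending on the imbalance and on how signs improve.

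These figures rest on assumed class shares, assumed grades, a borrowed 40% improvement rate and a score made of urinary items only. They show that the mechanism can matter; they do not estimate its size in this study. If the class mix is similar in the two cohorts, the problem disappears.

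It concerns a secondary outcome. The argument does not extend to the primary outcomes, remission and recurrence rates. It is a worthwhile, inexpensive improvement and not a fatal fault.

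**What to change.** In section 2.9, state that the cohorts are compared on the symptom score with a model containing both the baseline score and baseline clinical class, as a factor with the four levels of inclusion criterion 3. Apply the same terms to the repeated-measures analysis, and tabulate clinical class by cohort at baseline so that readers can see any imbalance.

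If urine protein or urine erythrocytes are also reported as separate improvement outcomes, say so in section 2.5.2. Analyse each in children who have that sign at baseline, and report new onset of a sign absent at baseline separately, as worsening.

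Class has to be established for eligibility, so no new data, visits or patients are needed. The factor uses three degrees of freedom, which is negligible with 250 per cohort. Component analyses would include fewer children. Class adjustment deals with this one imbalance only, not with confounding in general.
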